**Minimizing inactivity periods and increasing non-exercise physical activity in parents and their young children**

InPact study plan for ethics committee February 2011

Our physical activity level is determined by genetic (Pellegrini & Bjorklund 1998) and environmental factors (Gallahue & Ozmun 2006, Malina ym. 2004). Especially, learning physical activity habits from parental model has been shown to be influential (Sääkslahti 2005). Thus parents are in key position to influence children’s physical activity habits based on social cognitive theory of learning (Bandura 2002). On the other hand it has been reported that adults with young children are least active in Finland (Rovio et al. 2009). Thus, parents and their young children are the primary target of the present intervention study focusing especially on non-exercise physical activity.

By definition, physical activity is bodily movement that is produced by the contractile activity of skeletal muscle that substantially increases energy expenditure (ACSM). Heart rate (HR) elevation has been considered the prime response to physical activity and it is easily assessed even long periods of time. Heart rate recordings are typically used to evaluate cardiovascular response. However, HR is affected also by other factors than physical activity (Tulppo et al. 2003). Indeed, it is intriguing to think that HR and oxygen uptake are never zero, although person is not doing any physical activity (Fig. 1). On the other hand, muscle activation is prerequisite for physical activity but its role in quantifying physical activity level has been neglected. This study uses electromyography (EMG) to accurately measure muscle activity – and lack of activity – in ordinary people (Finni et al. 2007, Finni et al. 2010ab). Hypotheses on inactivity physiology paradigm that sitting is harmful for health even if person is considered to be physically active (Hamilton et al. 2007) can be readily examined with EMG measurements that reveal periods of sitting and quiet standing (Fig. 1). A report indicates that breaks in sedentary time independently of moderate-to-vigorous physical activity is beneficially associated with health indices such as BMI and triglycerides (Healy et al. 2008). Nationally this is very relevant issue, since 46% of women and 51% of men sit daily at least 6 hours (Sjöström et al. 2006).

Fig.1. Simultaneous recordings of HR and EMG from thigh muscles when standing quietly and during stair climbing and descend. HR response is very different from EMG in the repeated stair ascend. Inactivity periods are clearly identifiable for analysis of duration and frequency. Note that ascend with concentric muscle work requires more EMG activity and energy than eccentric muscle action during walking down.

**Purpose**

This study aims to show in a cluster randomized controlled trial (RCT) that simple actions to reduce time in sitting position are viable and that they have health-related benefits. Parents and their young children are the primary target of the study. After tailored physical activity counseling the parents commit themselves to the agreed behavioral changes during work, leisure time and weekends. In leisure time and on weekends the change in behavior will be guided to activate also the children.

**The main specific purposes and hypotheses are:**

1. To test what is the effectiveness of tailored counseling to minimize inactivity periods and increase physical activity in persons involved in sitting-related work. *H: Counseling increases physical activity and decreases muscle inactivity time during workday and leisure time*
2. To test if the counseling can induce long term behavioral changes that benefit health?

*H: Counseling induces behavioral changes that last long time. Positive effects in health related markers such as serum lipids and blood pressure can be seen at 6 and 12 months after counseling.*

1. To examine what is the effectiveness of parental counseling on children’s physical activity behavior? *H: There is transfer effect of parental counseling so that also the children’s physical activity has increased.*

**Methods**

**Design.** A cluster randomized controlled intervention will be performed on parents that sit more than 50% of the work time. The intervention group will receive tailored counseling to decrease time in sitting position and increase daily activity, especially the non-exercise activity. Children aged 3-8 will be included to the study and their physical activity will be objectively monitored before and three times after the parental counseling.

**Subjects.** Eligible participants are parents with work that primarily includes sitting. *Inclusion criteria*: healthy men and women with children 3-8 years old, and having work where they sit more than 50% of their work time. *Exclusion criteria*: self-reported chronic, long-term musculoskeletal disease or progressive neurological disease, diagnosed cardiovascular or metabolic disease with regular medication, families with pregnant mother at baseline, BMI>35, children confined to a wheelchair or bed. The recruitment will be performed in Jyväskylä region delivering advertisements to parents via kindergartens and primary schools. To avoid contamination of treatment the randomization will be done regionally before recruitment and the control group will not be informed about the intervention. Both the intervention and control groups will include areas from the city center and suburbs of Jyväskylä.

**Sample size.** From the preliminary results it can be expected that small changes in behavior can effectively decrease the longest inactivity periods and total inactivity time as example in Fig.2 shows. Based on decrease in the inactivity periods by behavioral changes the sample size of 10 would be sufficient to show statistically significant changes. However, we also aim that the intervention has significant health effects. Thus, it was estimated that increase of 0.2 mmol/l in high-density lipoprotein after 6 or 12 months of intervention can be possible with the intervention. The required sample size to show this effect would be 77. Adding the cluster effect (Cambell et al. 2004) and drop-outs we estimate that 100 subjects in both groups would be needed.

Fig 2. Histogram of daily muscle activity time (% of whole day activity) divided in sections 0-5% of maximum (MVC). Women n=6, 30 measurement days, men n=6, 26 measurement days. The women performed more non-exercise activity than men and it is significantly reflected to the main outcome. **p<0,01, ***p<0,001 (Haakana 2010).

**Ethics.** We will submit the study plan with questionnaires and informed consent for evaluation by the local ethics committee. The RCT will not begin before approval has been received. Subjects will be volunteers with right to withdraw from the study at any time without consequences. The study will be conducted according to good scientific practice.

**Protocol.** The protocol of the study is shown in Fig. 3. Before counseling the parents will be measured for baseline data (fasting blood samples, anthropometry, questionnaires, physical fitness test) and a representative normal day EMG activity with other measures of physical activity level. After counseling the representative day with agreed behavioral changes will be measured again using EMG and other devices for physical activity level assessment. In the first 3 months the compliance will be reinforced by phone calls and possible modifications to the agreed intervention will be made. Between 3 to 6 months the compliance will be followed once a month and no contact with the subjects will be made in the maintenance period. The midline and endline measurements include fasting measurements, questionnaires and 24-hour heart rate recordings. Control group participates only in baseline and normal day measurements, midline and endline measurements. Children will be measured at baseline, after 3, 6, 9 and 12 months for physical activity behavior using triaxial accelerometers (Actigraf).

Figure 3. Timeline of the project showing the timing of physical activity (PA) measurements for parents and children.

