After counseling the research personnel will phone the subjects two times to ask about the compliance of the goals set and send e-mails. This reinforcement period lasts 6 months. The end measurements at 12 months are made to assess the maintenance of the habitual changes and effects on health markers. During the last 6 months there will not be researcher contact other than 9 months measurements with the subjects.

The control group will not receive the counseling intervention but will undergo the measurements similarly as the intervention group. The counseling does not include dietary counseling. The subjects will be monitored for dietary changes by questionnaires but eating habits are assumed to be maintained the same.

**Statistical analysis**. The EMG activity variables such as total inactivity time during day and mean intensity of EMG will be used to categorize people into quartiles according to 1) physical activity and 2) health marker indexes. Chi Square will be used to compare EMG distributions and levels to other variables. The difference in physiological signals between categories will be compared using One-way/Multivariate ANOVA. Correlation and regression analysis will be used to retrieve relationships between physical and health conditions and physical activity assessments. Repeated measures ANOVA will be used to determine effects of intervention complemented with mixed model ANOVA in case of missing data points.

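### Eligibility lets several parents and children of one family enter, but the named analyses treat every person as independent

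*Protocol*

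**What the plan says.** Protocol, Methods, Subjects: eligibility is set per person, as "healthy men and women with children 3-8 years old" whose job is sedentary for over half of working hours. Under Design: "Children aged 3-8 will be included to the study and their physical activity will be objectively monitored". Neither sentence limits a family to one parent or one child. One exclusion is worded at family level: "families with pregnant mother at baseline".

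The text on the counseling intervention has the children, in the plural, wearing accelerometers from the time of the parent's baseline measurement. The counseling itself encourages activity that the whole family does together.

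Allocation is by area: "the randomization will be done regionally before recruitment". The Sample size paragraph adds an unspecified cluster effect and drop-out to a figure of 77 and arrives at 100.

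Protocol, Statistical analysis: "Repeated measures ANOVA will be used to determine effects of intervention complemented with mixed model ANOVA in case of missing data points". For the associations: "Correlation and regression analysis will be used to retrieve relationships between physical and health conditions and physical activity assessments". Chi-square tests and one-way or multivariate ANOVA are named for comparisons between categories. No term for family or for area appears, and the children's outcome has no analysis of its own.

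**The concern.** Siblings share a counseled parent and the same outings. That is the route by which the third hypothesis expects the intervention to reach them, so their changes in activity may well move together. Spouses share a home and leisure time. In their standard form, the named methods count each of these people as a separate piece of information.

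If families contribute several members, the number of subjects overstates the information. Intervals become too narrow, and an effect on children's activity is declared too often when there is none. Valid inference at area level would cover this in the comparison of arms. It would not by itself reach the correlations, regressions and category comparisons, because these do not compare arms.

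**Working it through.** **The plan's own figure.** The only allowance for clustering is in the Sample size paragraph, for HDL in parents. The 77 cannot be reproduced because the SD, significance level and power are not given. The step to 100 is a factor of 100/77 = 1.30 for clustering and drop-out together. With an assumed drop-out of 10%, 15% or 20%, the part left for all clustering, by area and by family, is:

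- 90/77 = 1.17
- 85/77 = 1.10
- 80/77 = 1.04

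The paragraph does not say which kind of cluster is meant, and nothing corresponds to it in the analysis.

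**Children, comparison of arms.** Inputs, all assumed because the protocol gives none:

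- f is the share of children with exactly one enrolled sibling.
- ρ is the sibling correlation of the quantity tested. In a repeated measures analysis the intervention effect is group by time. Stable similarity between siblings therefore cancels, and ρ is the correlation of their changes.

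Design effect: DE = 1 + f × ρ. The correct standard error is √DE times the one reported. Actual error rate of a nominal 5% two-sided test: 2 × [1 − Φ(1.96/√DE)].

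| f | ρ | DE | √DE | Actual error rate |
|---|---|---|---|---|
| 0 | any | 1.00 | 1.00 | 5.0% |
| 0.25 | 0.3 | 1.075 | 1.04 | 5.9% |
| 0.25 | 0.5 | 1.125 | 1.06 | 6.5% |
| 0.5 | 0.1 | 1.05 | 1.02 | 5.6% |
| 0.5 | 0.3 | 1.15 | 1.07 | 6.8% |
| 0.5 | 0.5 | 1.25 | 1.12 | 8.0% |
| 1 | 0.5 | 1.50 | 1.22 | 11.0% |

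At f = 0.5 and ρ = 0.3-0.5, 100 children carry the information of 100/1.15 = 87 to 100/1.25 = 80.

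A simulation with 200 children, half of them with a sibling, family correlation 0.3-0.5, 4-20 areas and no area effect gave 6.4-8.5% for the test that assumes independence. A family-robust test gave 4.5-5.4%. Leaving out the area effect isolates the family effect, so this does not describe the full design.

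**EMG-health slopes and correlations.** Here DE = 1 + f × ρx × ρe, where f is the share of adults whose spouse is also enrolled, and ρx and ρe are the within-couple correlations of predictor and residual (again assumed).

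| f | ρx | ρe | DE | Actual error rate |
|---|---|---|---|---|
| 1 | 0 | 0.3 | 1.00 | 5.0% |
| 0.5 | 0.3 | 0.3 | 1.045 | 5.5% |
| 1 | 0.3 | 0.3 | 1.09 | 6.0% (simulated 5.9%) |
| 1 | 0.5 | 0.5 | 1.25 | 8.0% (simulated 7.9%) |
| 1 | −0.2 | 0.3 | 0.94 | 4.3% |

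The bias is a product of two correlations. It vanishes if either is zero and reverses if their signs differ. No figure was computed for the chi-square or category comparisons.

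**The case against.** - **Enrolment.** A reader might infer that spouses and siblings will be enrolled. The protocol permits it but does not say so. The family-level exclusion is not evidence either way, since a pregnancy affects the household whichever parent takes part. The plural for the children makes sibling enrolment the natural reading, but not a stated fact. This objection stands, so the conclusion is conditional.

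- **The analysis plan.** Random effects and clustered standard errors are often left to a SAP, and none is shown. This carries some weight. However, the protocol does not leave the method open. It names subject-level repeated measures ANOVA and gives the mixed model a missing-data role only, and that choice errs if followed with several members per family.

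- **Area.** Households that live together fall within one randomised area, so inference at area level absorbs family correlation in the comparison of arms. This stands. For that comparison the absent area term is the larger gap, and family is secondary.

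- **Associations.** A reader might infer that the EMG-health standard errors are certainly too small. They are not. Both spouses must have sitting work and meet the health criteria, and both correlations must point the same way. The protocol's pilot histogram reports more non-exercise activity in women than in men, which would tend to lower the raw correlation within male-female couples. The point survives here only as a condition.

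**Conclusion.** The point holds conditionally. The eligibility text permits several members of a family, and the named analyses do not account for it.

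The children's analysis is the stronger part. At f = 0.5 and a sibling correlation of change of 0.3-0.5, intervals should be about 7-12% wider, and a nominal 5% test runs at about 6.8-8.0%. With no multi-member families the effect is nil. For the EMG-health associations, the positive correlations tried with half or all of the adults in enrolled couples give about 5.5-8%, and the bias can be nil or slightly reversed.

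Every f and every correlation is an assumption. The protocol does not support a claim that the error rates will in fact be inflated, only that nothing in the stated analysis prevents it.

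**What to change.** 1. Record a family identifier for every parent and child.
2. Fit the intervention model, for parents and for children, as a mixed model with a family effect nested in the randomised area, whether or not data are missing. The family effect should apply to change (family by time, or a family effect on baseline-adjusted outcomes), because a family intercept alone captures only stable similarity. Inference at area level also covers family clustering in the comparison of arms.
3. Use family-clustered standard errors, or a bootstrap over families, for the correlations, regressions and category comparisons.
4. Report the number of families beside the number of subjects.

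If only one parent and one child per family are meant to enter, a sentence saying so, with the rule for choosing them, settles the point instead.

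The cost is a change of analysis wording, an identifier that recruitment should already yield, and slightly wider intervals. No new measurements are needed.

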**Measurements**

[figure not shown]
**Short term main outcome is the physical activity (PA) behavior**. In parents it will be assessed with EMG, triaxial accelerometer and questionnaires. ***EMG*** will be measured using shorts with embedded textile electrodes (Suunto Oy, Vantaa, Finland / Megaelectronics Ltd., Kuopio, Finland) measuring activity from 4 thigh muscles during normal daily life and laboratory tests (Fig. 4). The measurement system has been tested for validity, repeatability and feasibility in our laboratory (Finni et al. 2007). The data is collected to a 52 g module in the waist in raw form with sampling frequency of 1000Hz. The raw EMG signal is rectified and averaged over 100 ms non-overlapping intervals. The signals are stored in a module for off line-analysis. The EMG data will be analyzed for inactivity period times and frequencies as well as for total inactivity. This analysis will be repeated using different signal levels (1%, 2%, 5% of maximum voluntary contraction) for detection of the inactivity periods. Activity histograms and on-off analysis will be performed. Burst analysis (Kern et al. 2001) will be used to quantify activity periods.

In a sub group of children we test the use of EMG shorts as measurement tool of physical activity.

Fig. 4. Shorts that are used to collect muscle EMG activity from thigh muscles.

***Acceleration.*** Triaxial acceleration will be collected during all the measurements (Alive heart monitor, Alive technologies, Australia) and be used to compare the activity counts with EMG levels for validation purposes. **In children** the PA behavior will be measured using triaxial accelerometer (Actigraf) that the children wear on their waist for one week at pre, 3, 6, 9 and 12 months after counseling intervention to parents. During this one week period, the parents will fill in diary of the childrens physical activities. In addition, children’s basic motor skills will be tested three times during the intervention.

***Questionnaires.*** From the detailed 7-day physical activity questionnaire focusing on non-exercise activity the daily MET values will be calculated for the past year at baseline and endline (modified from Lakka et al. 1997). During the days of data collection, the subjects fill in detailed physical activity diaries that reveal standing up from sitting position, walked up stairs etc.

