**Long term main outcomes are health-related indices and maintenance of the behavioral change.** Venous blood samples for whole blood count, blood lipids and glucose analysis will be taken in standardized fasting conditions in the mornings 7-9 am. Samples will be analyzed using standard methods in clinical use and also metabonomics. Serum will be stored for later analysis of other health related markers such as glucose and lipid metabolism (leptin, obestatin, glucagon-like peptide, C-peptide). DNA-samples will be taken from volunteers and leucocytes extracted for further analysis of associations regarding body composition and physical performance and activity. Blood pressure will also be measured in the morning. Anthropometry including body composition (dual X-ray absorbtiometry and bioimpedance, In-Body 720, Korea) in fasting condition, hip-to-waist circumference and BMI will be measured. Subcutaneous fat thicknesses from several sites will be measured using ultrasonography.

Heart rate will be measured with the same device as acceleration. Both time domain (e.g. RMSSD, SDNN) and frequency domain (Ultralow frequency <0.0033 Hz, Very Low frequency 0.0033-0.04 Hz, Low frequency 0.04-0.15 Hz and High frequency 0.15-0.4 Hz) analysis of HR variation (HRV) will be performed (Tulppo et al. 2003). Histogram of heart rate will be constructed. Hyvinvointianalyysi (Firstbeat Technologies, Finland) will be used to identify the time of physical activity, MET and stress-related decreases in HRV. The variables will be compared with EMG data and MET levels calculated from questionnaires. High frequency band has special meaning in determining cardiovascular health. Heart rate will be measured at baseline (before and after counceling), at 6 and 12 months.

Behavioral changes will be assessed using questionnaires that include questions such as: TV/computer time usage, time and places/facilities outdoors both alone and with family, way of commute, time in sitting position, subjective energy level etc.

**Background variables.** Background information of medication, chronic and acute diseases will be assessed in the screening process. Dietary records for 3 weekdays and 1 weekend day will be kept at baseline, midline and endline to evaluate whether similar diet has been maintained during the year as assumed. Questions regarding perceived health and wellbeing are included in the questionnaires. Physical fitness will be assessed with non-exercise questionnaire.

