**Field measurements during normal day.** The subjects will be well instructed for the use of HR-acceleration monitor and EMG-garments. The data will be collected continuously for waking hours during normal daily life, so that the two days of data collection are similar in all other respects except that during the second day the agreed intervention program is executed. Both days, subjects are requested to do a simple reference test containing lying down, sitting, quiet standing and stationary squat that is used to control the reproducibility of the EMG signal during the day. Each morning the data collection will be started at the laboratory by research personnel, and ended by the subject before going to bed except for heart rate recordings that will continue overnight.

**Counseling intervention.** Tailored counseling by trained research assistants will be targeted to decrease time in sitting position and increase non-exercise activity during workdays (commute and work time) and leisure time (evenings and weekends). This type of personal counseling has been shown to be effective (Leinonen et al. 2007). First, the subjects will be asked for the use of bicycle, car, elevator, stairs and walks during the day to identify items that can be modulated, e.g. standing in coffee breaks, walking about while talking to phone, taking a walk before lunch etc. Leisure time habits will be asked and changes in habits are suggested such as walk to library instead of watching TV, going to visit neighbor by foot instead of calling on the phone. The items that the subjects are willing to modify will be written down and an agreement document will be signed by the subject and researcher to confirm the intended changes in behavior. Subjects will be motivated to this change by showing graphs such as Fig.1 and explaining the importance of muscle activity and pointing out long inactivity periods when one is sitting. Counseling includes encouragement toward family physical activities during leisure time (visiting playgrounds, swimming halls, parks and forests etc.) utilizing material from www.perheliikunta.net.

The counseling will take place about after 1 week of the baseline measurements. Starting from the parent’s baseline measurement the children will wear the accelerometers for 1 week. After this there will be the counseling and after 1 week from counseling the measurements for parents wearing EMG garments will be repeated on the same weekday as the baseline measurement.

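### The protocol gives two conflicting accounts of how many EMG days the control parents have; the narrower one would leave the EMG outcome with no control value after baseline

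*Protocol*

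**What the plan says.** The Protocol paragraph of Methods sets out the parents' schedule. Before counseling there are baseline data and one representative normal day with EMG. The next EMG day is described separately: "After counseling the representative day with agreed behavioral changes will be measured again using EMG". Compliance contacts follow. The later visits are then defined: "The midline and endline measurements include fasting measurements, questionnaires and 24-hour heart rate recordings". The next sentence is about controls: "Control group participates only in baseline and normal day measurements, midline and endline measurements".

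The text that closes the counseling intervention, just before Statistical analysis, says that controls receive no counseling but "will undergo the measurements similarly as the intervention group".

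Three other places bear on the question:

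- Field measurements during normal day describes both EMG days under that one heading and intends that "the two days of data collection are similar in all other respects except that during the second day the agreed intervention program is executed".
- Counseling intervention dates the repeat: "after 1 week from counseling the measurements for parents wearing EMG garments will be repeated on the same weekday as the baseline measurement".
- The heart rate text under the long-term outcomes says "Heart rate will be measured at baseline (before and after counceling), at 6 and 12 months".

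**The concern.** In the Protocol paragraph the term *normal day* has one antecedent, the EMG day before counseling. The day after counseling is described in different words, and the control sentence then sets a limit with the word *only*. A research assistant working from that paragraph would give a control parent one EMG day. One working from the end of the counseling text would give two.

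The first hypothesis includes a fall in muscle inactivity time, which is what EMG measures. EMG is also the first instrument named for the short-term main outcome in parents. The section on expected results says that the effect on muscle activity will come from the randomized controlled study. With a single control EMG day there is no control change to set against the intervention change, and the repeated measures ANOVA named under Statistical analysis has no group-by-time contrast for EMG. A day that was never recorded cannot be recovered later, so a SAP cannot settle this; the measurement schedule has to.

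**Working it through.** The plan states no figure to reproduce on this point. The check is a comparison of the texts, followed by a count and one illustration.

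**Step 1. EMG days per parent, by source**

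| Source | Intervention | Control |
|---|---|---|
| Methods, Protocol paragraph, read literally | 2 | 1 (the normal day) |
| End of the counseling text | 2 | 2 (measured like the intervention arm) |
| Midline and endline as listed in Methods | no EMG listed | no EMG listed |

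The second day is therefore the only EMG measurement after baseline that the text describes. Control EMG days after baseline: 1 − 1 = 0 on the first reading, 2 − 1 = 1 on the second.

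**Step 2. Can the other text decide between the two readings?** The second EMG day is defined in Methods by the agreed changes and in Field measurements by carrying out the programme, and it is dated in Counseling intervention by the counseling session. Controls have none of these. The available text therefore does not name a second control day outright. The heading that covers both field days, and the heart rate sentence that counts before and after counseling as baseline, allow two days but do not mention the control arm.

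**Step 3. Which measures are affected?** Heart rate is recorded at midline and endline, with the same device as acceleration, and "Triaxial acceleration will be collected during all the measurements". Questionnaires are also listed at those visits. These measures give controls values after baseline on either reading. The doubt is confined to EMG.

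**Step 4. Matching date for controls.** Counseling comes about 1 week after baseline and the repeat 1 week after counseling: 1 + 1 = about 2 weeks after baseline, on the same weekday.

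**Step 5. Illustration of what a control day protects against.** Assumptions: 100 intervention parents (the planned group size), a two-sided 5% test, clustering ignored, no counseling effect, and a difference of *d* SD of the change between the two days for other reasons. The documents give no value for *d*, so a range is shown. The one-sample t-test has 99 degrees of freedom, critical value 1.984 and noncentrality d√100 = 10d. The between-arm test compares change in 100 against 100 with the same shift in both arms (20,000 simulated trials per shift).

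| Shift d | Noncentrality | Before-after test significant | Between-arm test of change significant |
|---|---|---|---|
| 0.1 | 1.0 | 16.8% | 5.2% |
| 0.2 | 2.0 | 50.8% | 4.8% |
| 0.3 | 3.0 | 84.4% | 4.7% |

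The plan does not propose a within-arm test. The table shows only why a before-after change is weaker evidence than a difference between arms.

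**The case against.** The best case for the plan is that two control days were always meant. The statement at the end of the counseling text is the one that sets out directly what controls do and do not receive, and it follows soon after the sentence about repeating the EMG measurement. The Methods sentence speaks of normal day measurements in the plural, and the field-measurement heading uses *normal day* for both days. The word *only* comes straight after the compliance contacts and the midline and endline visits, and may exclude no more than those contacts. A repeated measures analysis of the intervention effect fits two control days. Fig. 3 is the protocol's own timeline for the physical activity measurements and may show the control day and its date.

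Most of this stands. It makes the two-day reading plausible, and it rules out two stronger claims that a reader might infer. One is that the trial plans no second control EMG day: the documents do not show that, since one of the two statements says the opposite. The other is that the protocol never dates that day: this cannot be said while the timing figure is unseen. Nor is the whole short-term main outcome at risk, because EMG is one of three kinds of instrument named for it and the other two are not in doubt.

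What does not stand is that no change is needed. Even if the figure shows two control days, the limiting sentence in Methods would still disagree with it and with the end of the counseling text.

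**Conclusion.** The conflict is real and should be corrected. It is an ambiguity more than a flat contradiction. Followed literally, the Methods sentence gives controls 0 EMG days after baseline; followed as the end of the counseling text has it, 1. In the first case the EMG part of objective 1 would rest on the intention that the two days differ only by the programme, with no concurrent control to check it.

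The conclusion rests on two things: that *normal day* in Methods means the day before counseling, as its use in that paragraph suggests, and that EMG is not measured at midline or endline, where it is not listed. The percentages above are illustration only; neither the shifts nor the test comes from the plan. Confidence is medium, because the unseen figure may show that two days were intended.

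**What to change.** Replace the limiting sentence in the Protocol paragraph of Methods with:

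*Control parents undergo all measurements at the matching times, including the second EMG, heart rate and acceleration day (same weekday, about 2 weeks after baseline, as a usual day), but receive no counseling or compliance contacts.*

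Check that Fig. 3 agrees with it. If two control days were meant, the cost is this one sentence. If one day was meant, the cost is one further EMG day for up to 100 control parents. If that day will not be collected, say so in the protocol and report the EMG result as an uncontrolled before-after change, not as a randomized effect.
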